### Subgroup analyses

The properties of the s-MoCA-SWE will be evaluated further. Subgroup analysis will be performed by studying the differences between patients with and without a previous stroke/TIA, with the hypothesis that patients with a previous stroke are more likely to have impaired cognition; by stroke severity, with the hypothesis that patients with more severe stroke are more likely to have more impaired cognition; and by age, with the hypothesis that older patients are more likely to have impaired cognition.

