### Study sample

The Väststroke dataset comprises data on 6493 patients; the EFFECTS dataset comprises data on 1500 patients (online supplemental figure). The two datasets will be aligned.

10.1136/bmjopen-2021-049035.supp1Supplementary data

The inclusion criteria are as follows:

Age ≥18 years at stroke onset.A diagnosis of stroke according to the International Classification of Diseases-10: intracerebral haemorrhage (I61), cerebral infarction (I63) and stroke, not specified as haemorrhage or infarction (I64).Patients with a previous stroke and/or transient ischaemic attack (TIA).A complete MoCA (0–30 p).

The exclusion criterion was as follows:

Duplicate registration on the Väststroke and EFFECTS datasets (duplicates will be removed from the Väststroke dataset).

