### Study variables

Only the variables available in both the Väststroke and EFFECTS datasets will be used. Detailed information on all variables that will be included in the study, their categories, and coding for the merged datasets are presented in online supplemental table 1.

The MoCA is a valid and reliable instrument for cognitive screening in the acute and subacute phases of stroke.^8–10^ The total MoCA score ranges between 0 and 30 points (p); 1 p for a maximum of 12 years of education can be added to the total score. A score of ≤25 p indicates cognitive impairment.^8^ MoCA items were registered in the datasets as follows:

Orientation (range, 0–6 p).Delayed recall (range, 0–5 p).Visuospatial/executive functions (range, 0–5 p): trial (1 p)+cube (1 p)+clock (3 p).Naming of three animals (range, 0–3 p).Digit span, two tasks (range, 0–2 p).Repetition of two sentences (range, 0–2 p).Categories, two tasks (range, 0–2 p).Serial 7 (range, 0–3 p).Fluency (range, 0–1 p).Tap on A (range, 0–1 p).

Stroke severity at onset was assessed using the National Institutes of Health Stroke Scale (NIHSS).^28^ The NIHSS comprises 15 items with varying score ranges per item. The total NIHSS score is 0–42 p, with a higher score indicating a more severe stroke.^28^

Reperfusion treatment will be categorised as both thrombolysis and thrombectomy, only thrombolysis or only thrombectomy.

Information about a previous stroke and/or TIA was recorded (yes, no or unknown). The Väststroke register comprises patients with a first-ever stroke, however, patients with previous TIA were included. In the EFFECTS study, patients could have a prior stroke and/or TIA, and these two conditions could not be distinguished.

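### The previous stroke/TIA subgroup cannot test a hypothesis about previous stroke: a positive history means TIA only in Väststroke, and stroke and/or TIA in EFFECTS

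*Protocol article*

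**What the plan says.** All references are to the Protocol article.

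- **Subgroup analyses.** The planned comparison is between "patients with and without a previous stroke/TIA, with the hypothesis that patients with a previous stroke are more likely to have impaired cognition". The section mentions neither stratification by dataset nor restriction to one of them.
- **Study variables, coding.** There is one composite item: "Information about a previous stroke and/or TIA was recorded (yes, no or unknown"). The section also states: "Only the variables available in both the Väststroke and EFFECTS datasets will be used".
- **Study variables, Väststroke.** "The Väststroke register comprises patients with a first-ever stroke, however, patients with previous TIA were included".
- **Study variables, EFFECTS.** "In the EFFECTS study, patients could have a prior stroke and/or TIA, and these two conditions could not be distinguished".
- **Study sample, sizes.** "The Väststroke dataset comprises data on 6493 patients; the EFFECTS dataset comprises data on 1500 patients". These are counts before duplicates are removed and before the complete-MoCA criterion is applied.
- **Study sample, inclusion criteria.** One bullet reads "Patients with a previous stroke and/or transient ischaemic attack (TIA"). It stands beside the bullets on age, stroke diagnosis and a complete MoCA.
- **Study procedure.** In Väststroke, occupational therapists who have regular workshops and peer reviews gave the MoCA. In EFFECTS it was given by nurses, physicians or other study personnel without formal training in it, and sometimes a local occupational therapist's assessment was used.

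**The concern.** The contrast is defined on stroke/TIA, but the hypothesis attached to it is about previous stroke. The protocol's own description of its two sources shows that the data cannot isolate that exposure.

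A second problem follows from pooling. The *no* group means the same in both sources (neither event), but the *yes* group does not. Unless the share of *yes* happens to be equal in the two datasets, having a history is also associated with coming from one dataset rather than the other. The datasets differ in selection (a register of three units at one hospital against a randomised trial in 35 units) and in who administered the MoCA.

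At stake is how this subgroup result is interpreted. A null result could reflect dilution by TIA, and a positive or negative one could reflect the dataset. Either could be read as a finding about previous stroke.

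**Working it through.** The plan gives no sample size, power or event figure for this subgroup, so there is no stated figure to reproduce. The finding rests on setting the sections side by side. The arithmetic only shows how little the document fixes.

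**1. What each value means**

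| | Väststroke | EFFECTS |
|---|---|---|
| *yes* | TIA only | stroke, TIA or both, not separable |
| *no* | neither | neither |
| could a previous stroke be present? | no | yes, but not identifiable |

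No cell identifies previous stroke. Restricting to EFFECTS gives one consistent definition but still does not separate stroke from TIA.

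**2. Where previous strokes can come from**

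With V = 6493 and E = 1500, the EFFECTS share is 1500 / (6493 + 1500) = 1500 / 7993 = 18.8%. The other 81.2% can contribute only TIA to the *yes* group.

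**3. Make-up of the pooled *yes* group (illustration)**

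The following inputs are assumed and are not in the document: q = previous TIA in Väststroke, 3% to 10%; r = *yes* in EFFECTS, 10% to 30%; s = share of EFFECTS *yes* with a true previous stroke, 50% to 100%.

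Previous-stroke share = E·r·s / (V·q + E·r)

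- Lowest (q 10%, r 10%, s 50%): 75 / (649.3 + 150) = 9.4%
- Middle (q 5%, r 20%, s 75%): 225 / (324.65 + 300) = 36.0%
- Highest (q 3%, r 30%, s 100%): 450 / (194.79 + 450) = 69.8%

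**4. Dilution (illustration)**

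Further assumptions: previous stroke raises the proportion impaired by 10 percentage points, TIA has no effect, and base rates are equal in the two datasets. The pooled difference is then 10 × share: 0.9 points at the lowest setting, 3.6 at the middle and 7.0 at the highest.

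**5. Dataset difference with no true effect (illustration)**

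Assume a 10-point difference in base rate, Väststroke 60% and EFFECTS 50% impaired. At the middle setting:

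- *yes*: (324.65 × 0.60 + 300 × 0.50) / 624.65 = 55.2%
- *no*: (6168.35 × 0.60 + 1200 × 0.50) / 7368.35 = 58.4%
- difference: −3.2 points, against the hypothesis

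With the base rates reversed (50% and 60%), the difference is +3.2 points. Two other settings give 1.5 points (q 10%, r 20%) and 5.6 points (q 3%, r 30%), again with either sign. If q equals r, this component vanishes.

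**6. Both together, middle setting**

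A true 10-point effect would appear as 3.6 − 3.2 = 0.4 points or 3.6 + 3.2 = 6.8 points, depending on which dataset has the higher base rate. The document does not say which applies.

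**The case against.** The strongest reply is that the planned contrast is correctly labelled stroke/TIA, that *previous stroke* in the hypothesis may be shorthand for the composite just named, and that Study variables openly states each source's limits. The study is exploratory, this is one of three supplementary subgroup comparisons, and the merged coding is in a supplementary table that is not shown. Stratification or adjustment for dataset may be specified elsewhere.

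Much of this stands, and it limits the severity. It does not remove the point. If the wording is shorthand, it should be corrected, because on the protocol's own account the two exposures differ. No coding table or later analysis detail can recover a distinction that the sources did not record.

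Three stronger readings are tempting but not supported:

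- **The inclusion bullet contradicts the first-ever-stroke register, or would remove most of the sample.** Väststroke patients with a previous TIA satisfy the bullet. The yes/no/unknown coding and the planned comparison group without such a history both presuppose that patients without earlier events are included. The bullet is therefore most plausibly permissive. It is unclear, not contradictory.
- **The datasets differ in timing of assessment.** The protocol gives a 2 to 15 day enrolment window for EFFECTS but no separate window for Väststroke, and describes screening overall as acute and early subacute. Only the differences in raters and selection are documented.
- **The bias has a particular size or sign.** Any single figure depends on history rates and base rates that the document does not give, and on counts taken before a complete-MoCA restriction for which many non-random missing values are expected.

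**Conclusion.** The point holds in limited form. From the protocol's own wording, without any assumption, the previous-stroke hypothesis cannot be tested with the data described, and an unstratified pooled contrast combines two exposure definitions with dataset differences in selection and MoCA raters.

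The size and direction of the resulting bias cannot be determined from the document. The illustrative ranges (previous-stroke share of 9% to 70%; a 10-point effect appearing as 0.9 to 7.0 points; a spurious 1.5 to 5.6 points of either sign) rest entirely on the assumed inputs and show only that the result would be hard to interpret.

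Severity is minor to moderate. A reader might infer that the short form itself is compromised. It is not: item selection, the cut-off and the comparison with the other short forms do not use this variable.

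**What to change.** 1. **Hypothesis (Subgroup analyses).** Restate it as concerning previous stroke and/or TIA, so that it matches the contrast and the recorded variable.
2. **Analysis.** Present this subgroup by dataset: EFFECTS labelled *previous stroke and/or TIA*, Väststroke labelled *previous TIA*. If one combined estimate is wanted, stratify by dataset and do not report a single unstratified pooled contrast. Stratifying deals with the dataset difference but not with the difference in exposure definition, so the two labels should still be shown. State that previous stroke alone cannot be isolated, even within EFFECTS.
3. **Inclusion bullet (Study sample).** As a minor clarification, reword it to *with or without a previous stroke and/or TIA*. Read literally as a requirement, it would empty the comparison group that the subgroup analysis needs.

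The cost is a few changes of wording, no new data, and smaller groups with less precision (at most 1500 patients in the EFFECTS analysis).

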### Missing data

For descriptive statistics, data on all included patients will be used. The proportion of missing values will be provided for each baseline variable.

### Statistical software

Data will be analysed using SPSS Statistics for Windows V.27.0 (released on 2018; IBM) and R V.4.0.2 (R Core Team. R: A language and environment for statistical computing. R Foundation for Statistical Computing, Vienna, Austria.).

### Patient and public involvement statement

The patients and the public were not involved in the design of the protocol.

Cognition has been identified by patients, their caregivers, and healthcare professionals as one of the most important research areas in stroke.^35^ Furthermore, many patients have reported unmet needs regarding problems with cognitive functions, such as memory, concentration and speaking/reading.^36^ Thus, early identification of cognitive impairment is important.

Patients with stroke can find cognitive assessments fairly burdensome in acute stroke and would prefer short tests if possible. By developing s-MoCA-SWE, we hope to have a simpler and more efficient cognitive screening tool that can be used during acute and subacute stroke. Theoretically, this would lead to a higher proportion of patients who receive the recommended cognitive screenings.

## Ethics and dissemination

Väststroke: The study obtained ethics approval from the Regional Ethical Review Board in Gothenburg (346–16) and the Swedish Ethical Review Authority (amendment 2019–04299). According to the Swedish Data Protection Authority, the handling of data generated within the framework of quality registers represents an exception to the general rule of written informed consent being required from patients. Furthermore, the Personal Data Act (Swedish law #1998:204, issued 29 April 1998) allows data from medical charts to be collected for clinical purposes and quality control without written informed consent.

The EFFECTS study has received ethical approval from the Stockholm Ethics Committee (2013/1265-31/2 on 30 September 2013). All participants of the EFFECTS study provided written consent for inclusion in the randomised controlled trial. They also provided written and oral consent to merge their data with other registry data.

In order to disseminate the study findings to a wide audience, results will be published in international, peer-reviewed journals, presented at local and international conferences, communicated to clinical practitioners in local meetings and seminars and shared via social media channels.^37^ Furthermore, a short report will be published in Swedish journals that target professionals who perform clinical cognitive screenings.
